## Abstract

**Background:**

The prevalence of chronic and complex pediatric health conditions has quickly risen over the last decades. Chronic and complex health conditions make pediatric patients and their families more susceptible to many distressing events during their lifespan. Mindfulness-based interventions have become a popular intervention for individuals living with chronic illnesses and have been adapted for pediatric populations with good results, including online versions. This study intends to report an implementation protocol of an online mindfulness-based program for adolescents to address an important gap in stress relief and health promotion for pediatric patients.

**Methods:**

In this article, we describe the rationale and design of an implementation study of an online mindfulness-based program for pediatric patients at a tertiary pediatric hospital in South America. Participants will be recruited during one year to participate in an eight-session online mindfulness-based program. To assess our primary aim of feasibility, we will exam recruitment, retention and participation rates. Participants will also complete a symptomatology evaluation (i.e., depression, anxiety, and stress symptoms) at baseline and immediately at post-treatment and fidelity will be evaluated by a structured questionnaire.

**Discussion:**

This study will be the first known to assess the implementation of an online mindfulness-based program for a pediatric population at a tertiary pediatric center in South America under real-life conditions. This study will establish the feasibility of a novel intervention aimed at promoting mental health and positive coping strategies among pediatric patients with chronic and complex health conditions. Evidence from this study would be useful to patients, families, clinicians, and policymakers and will help to devise strategies of health promotion for the pediatric population, as well as serve as a model for a future trial to examine efficacy of the proposed intervention.

**Trial registration:**

This research has been registered at Ensaiosclinicos.gov.br, identifier RBR-23trp87. Registered 25 February 2022—retrospectively registered.

## Background

The prevalence of chronic and complex pediatric health conditions has quickly risen over the last decades [1]. These conditions are usually associated with a long-term or lifelong treatment, numerous hospitalizations, and severe treatment side effects, making these patients and their families more susceptible to a number of distressing events [2]. The conventional health system has favored disease-centered care, which is poorly aligned with the current need for a patient-centered care. This scenario creates the demand for a change in the way patients are treated, with a special attention to health and wellness promotion Multidisciplinary healthcare models that implement integrative and complementary therapies for patients with chronic illness have demonstrated some promising results [3].

The field of integrative pediatrics represents an evolution in pediatric conventional care and is defined by patient and family-centered care in the context of community, focus on prevention and health promotion, adoption of evidence-oriented practices, and the use of all appropriate options to treat children as a whole—mind, body, and spirit. The field has grown at a fast pace in the past decade in response to a number of gaps left by the conventional healthcare system [3, 4].

There are five major domains of Complementary and Alternative Medicine, according to the National Institute of Health’s National Center: mind-body medicine, biologically based practices, manipulative and body-based practices, whole medical systems. The field of mind-body medicine aims to integrate thoughts, emotions, and physiologic processes to promote integral health. Mind-body therapies have special value in addressing pain, fear, and stress that accompanies many pediatric patients during their life. The most recognized mind-body therapies, which can be used alone or blended with conventional treatments, are mindfulness, yoga, technology-assisted relaxation approaches, and clinical hypnosis. These therapies may address a number of different clinical conditions: childhood stress and trauma; acute, chronic, and perioperative pain; mental health disorders; behavioral and developmental issues; and autoimmune illness [5].

This study will report an implementation protocol, which will examine the feasibility and fidelity of an eight-session online mindfulness-based program for pediatric patients. As an exploratory outcome, we will examine the intensity of mental health symptoms (e.g., symptoms of depression, anxiety and stress) pre- and post-intervention. This protocol aims to address a critical gap in the implementation of mental health promotion programs for pediatric chronic and complex patients of a tertiary pediatric health center in South America.

## Methods

### Design overview

This single-arm, open-label, pilot trial will examine implementation outcomes (feasibility, fidelity, patient’s symptomatology) of an eight-session mindfulness-based program for pediatric patients with chronic and complex health conditions. The intervention will include eight online individual sessions targeting content adapted from traditional mindfulness-based interventions (MBIs). The flow of procedures has been outlined in Fig. 1.

**Fig. 1 Fig1:**
[figure not shown]
Flowchart of study procedures

### Study setting

This study is being conducted at the Institute of Children and Adolescents of the Faculty of Medicine of the University of São Paulo, Brazil. We approached clinical divisions regarding their interest and readiness to participate in the study. The Ethics Committee of the Faculty of Medicine of the University of Sao Paulo approved the study under the number 88714018.0.0000.0068 in May 2018. The Ethics Committee renewed the approval in August 2020.

### Participants

Inclusion criteria for study enrollment are (i) pediatric patients aged 12 to 18 years old in treatment at the Institute of Children and Adolescents of Hospital das Clinicas of the University of São Paulo; (ii) caregiver consent/adolescent assent; (iii) internet access at home; (iv) adolescent’s self-declared state of stress or the will to develop coping strategies. The exclusion criteria for the study are (i) a confirmed psychiatric condition by the time of recruitment; (ii) the refuse to participate.

Patients are eligible if they are at follow-up treatment at the Institute of Children and Adolescents during the study period.

### Recruitment, screening, and enrollment

Medical providers and other clinic staff will be informed about the study and will be able to refer interested patients to the research team. Patients will be recruited for 1 year.

Interested patients will be screened by phone contact for eligibility. Eligible patients will be asked to sign the consent and assent form after it is reviewed with research staff (study procedures, potential risks and benefits of study involvement, rights to withdraw from the study). All participants will receive a copy of the signed document. In addition, demographic information will be collected.

Eligible participants enrolled in the program will be scheduled for their first session approximately 1 to 4 weeks later. In the first session, patients will be asked to complete a baseline symptomatology assessment.

### Study intervention

The Being Mindful® program (Be.M®) was specially developed for the Brazilian pediatric population concerning social, cultural and language specificities. The Be.M® adopts universal mindfulness and compassion principles, which are also part of other mindfulness-based interventions: focused attention meditation (attention to body and breathing), open monitoring attention (attention to emotional tone, thoughts, and self-awareness), loving-kindness meditation, and mindful movements [7, 8, 39, 40]. The content is in Portuguese, and the vocabulary and activities were adapted for the Brazilian cultural background.

The eight sessions will be delivered individually to each patient enrolled using a video-conference platform and will be held by qualified mindfulness instructors. Participants will receive a proper explanation and recreational activities related to the subject of interest, as well as formal meditation practices. The program material is available on a website platform (www.projetobem.com.br), which offers: six content videos, ten guided meditation practices and six workbooks in PDF format to be downloaded. An overview of the Be.M® Program contents can be seen in Table 1.

**Table 1 Tab1:** Program description of the Being Mindful® Program for pediatric patients

Titles	Contents	Concepts
What is mindfulness?	- Definition of mindfulness concepts-informal mindfulness practices-definition of mindfulness meditation practices - The practice of mindfulness meditation	- Agitated mind model - Meditation anchor: the five senses - Ability developed: focused attention
Attention to the body	- Paying attention to the body - Mindful movements—how do I know if I am meditating?	- Mindful body - Meditation anchor: the body and body movements - Abilities developed: focused attention, attention regulation
Attention to the breath	- Paying attention to the breath - Breath movements - Belly-breathing	- Mindful breathing—meditation anchor: breathing movements—the relaxation response - Abilities developed: focused attention, attention regulation
Accepting emotions	- Acknowledging and accepting all emotions - Dealing with difficult emotions - Feeling emotions in the body - Emotions are like the weather forecast	- Mindful emotions - Meditation anchor: feeling emotions in the body - The concept of impermanence - Abilities developed: open monitoring attention; emotional regulation
Making a pause	- Making a pause is important - Acting instead of reacting—a pause can help you cultivate wellness	- Being mindful - Meditation: integrating all (self-observer practice) - Automatic pilot model - Abilities developed: open monitoring attention; self-awareness, and self-kindness
A safe place	- Connecting mind-body with kindness - The connection between all of us - Being kind to yourself and others - Finding your safe place	- Loving-kindness - Compassion - Shared humanity - Resilience - Meditation: Loving-kindness practice - Abilities developed: self-kindness; selfcompassion

### Intervention content

#### Session 1: introduction and background

Participants and their parents will be provided with instruction on the program guidelines (e.g., confidentiality, respect, privacy and rules of canceling and rescheduling) and an overview of the purpose and structure of the program. Parents will be invited to get familiar with the Be.M® website (www.projetobem.com.br), in order to support their children. As a home exercise, participants will be asked to complete an online questionnaire to evaluate symptoms of depression, anxiety and stress before the program starts.

#### Session 2: what is mindfulness?

Participants will be given an explanation on the definition and concept of mindfulness and mindfulness meditation practices. Education on the benefits of paying attention to the present moment will be discussed. In this session, participants will be oriented to explore the present moment using the five senses (e.g., touch, sight, sound, smell, and taste). Participants will be asked to take a moment to drink a glass of water with full attention to the present moment using the five senses. For home practice, participants will be encouraged to listen to *Meditation 1* and to engage in the following mindfulness activity: “Choose a routine activity (e.g., taking a shower, washing your hands, eating or drinking) and do it mindfully using your five senses, as a way to be in the present moment.”

#### Session 3: attention to the body

Participants will be encouraged to share their impressions about the home practice from previous session. They will be given an explanation about the difference between meditating and other types of activities and how to realize if someone is meditating. Education on the benefits of paying attention to the present moment will be discussed. In this session, participants will be oriented to explore the present moment using their body, especially with mindful movements. Participants will be asked to take a moment to move their neck and shoulders gently paying full attention to the body and the present moment. For home practice, participants will be encouraged to listen to *Meditation 2* and to engage in the following mindfulness activity: *“Choose a person to be with you in this activity. Hold hands with your partner and pay full attention only to your hands for some moment: the position, touch and temperature. Just feel your body.”*

#### Session 4: attention to the breath

Participants will be encouraged to share their impressions about the home practice from previous session. They will be given an explanation about the mindful breathing and the concept of Relaxation Response. Education on the benefits of paying attention to the present moment will be discussed. In this session, participants will be oriented to explore the present moment using their breath movements. Participants will be asked to take a moment to feel their breathing movements in their belly. For home practice, participants will be encouraged to listen to *Meditation 3* and to engage in the following mindfulness activity: “Put your hands in your belly and feel the movement of the breath in your belly. You can count from 1 to 10 and repeat this procedure as much as you like.”

#### Session 5: accepting emotions

Participants will be encouraged to share their impressions about the home practice from previous session. They will be given an explanation about how to feel emotions in the body and how to deal with difficult emotions. Education on the concept of impermanence will be discussed. In this session, participants will be oriented to feel their emotions in the body in the present moment. Participants will be asked to take a moment to feel their emotions and draw it as a weather forecast. For home practice, participants will be encouraged to listen to *Meditation 4* and to engage in the following mindfulness activity: “Pay attention to your body and try to identify your emotions in the present moment, without judging or the need to chance anything.”

#### Session 6: making a pause

Participants will be encouraged to share their impressions about the home practice from previous session. They will be given an explanation about the automatic pilot mode. Education on the concept of “acting instead of reacting” will be discussed. In this session, participants will be oriented to understand the importance of making a pause to cultivate peace and wellbeing. Participants will be asked to remember a situation in which a pause would have helped them to stay calm and make a better choice. For home practice, participants will be encouraged to listen to *Meditation 5* and to engage in the following mindfulness activity: “Choose an activity that you do in automatic pilot mode and do it differently than you are used to, so you can realize how to stop the automatic pilot mode and make better choices for you.”

#### Session 7: a safe place

Participants will be encouraged to share their impressions about the home practice from previous session. They will be given an explanation about the concept of loving-kindness. Education on the practice of loving-kindness to themselves and others will be discussed. In this session, participants will be oriented to understand the importance of connecting mind and body with kindness, in order to find an inner place of peace and wellbeing. Participants will be asked to say or write kind words to themselves and to another person of their choice. For home practice, participants will be encouraged to listen to *Meditation 6* and to engage in the following mindfulness activity: “Try to draw or write about your SAFE PLACE: a place where you can be kind to yourself and feel calm; a place where you can always go when things get difficult for you.”

#### Session 8: review and wrap-up

Skills learned in the previous sessions will be reviewed and specific plans for the maintenance of a mindful life will be discussed. Participants will be asked to complete a post-treatment online questionnaire to evaluate symptoms of depression, anxiety and stress and provide feedback on the program.

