#### Fidelity

The secondary outcome will be fidelity, defined as the degree to which an intervention was implemented as prescribed in the original protocol [41]. Fidelity is a key element to move treatments from the clinical lab to real-world delivery systems [42]. It can be measured through self-report, ratings, or direct observation. In this study, fidelity will be determined with an implementation form (Table 2), that will be filled by the two mindfulness instructors after the intervention is completed. A score below 40% will indicate low fidelity to the original protocol, a score between 40% and 70% will indicate moderate fidelity and a score higher than 70% will indicate high fidelity to the original protocol.

**Table 2 Tab2:** Implementation form

1. Did the family/patient sign the *Informed Consent Form*?	Yes/No
2. Was the family invited to get familiar with the program by accessing the online material available on the website?	Yes/No
3. Did the patient receive the graphic material before the first session?	Yes/No
4. Did the family/patient receive the password for online material before the first session?	Yes/No
5. Was the “task agreement” sent to the family before the first session?	Yes/No
6. Was the pre-test DASS answered right after the first session?	Yes/No
7. Were all sessions delivered on a video-conference platform?	Yes/No
8. Was the program delivered in 8 sessions, twice a week?	Yes/No
9. Did each session last between 30 and 60 min?	Yes/No
10. After 4 weeks, how many sessions had been delivered?	8 /less than 8
11. How many sessions did the patient miss during the program?	0/1/2/3/4/5/6/7/8
12. Was the program finished?	Yes/No
13. Was the post-test DASS answered right after the final session?	Yes/No
14. Was the program provided by a trained mindfulness instructor?	Yes/No
15. Where was the patient recruited to the program?	Inpatient unit/outpatient unit

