### Data analysis

As this is a pilot feasibility trial, a sample size calculation is not appropriate. Given time and logistical constraints, our aim is to recruit as much patients as possible over a 1-year period. A sample of 40 participants recruited is expected to achieve the goal of 30 participants who complete the study, which may be sufficient to provide useful information about the feasibility of the protocol [46, 47].

Baseline data on all enrolled patients will be summarized using descriptive statistics. Feasibility will be analyzed to compare all eligible patients with those enrolled and those who completed the program with complete measurements collected. Fidelity will be classified according to the score measured by the implementation form.

Comparison tests of two means will be performed on the DASS 21 score. The comparisons will be made with ANOVA repeated measures analysis or with the non-parametric equivalents as appropriate. The descriptive and inferential statistics will be two-tailed, will be reported with 95% confidence intervals and will use *p* values at an α = 0.05 level of significance.

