Forth, we will be assessing outcomes only at immediate post-intervention, which may be insufficient to address long-term effects. And finally, given recruitment occurs across different pediatric sub-specialties’ populations, variations in sample characteristics may impact the outcomes of interest for this study.

In the future, the idea is to exam the efficacy of this intervention in a larger and more rigorous trial, considering all adaptations needed based on this pilot study, which would provide a better understanding of how mindfulness might influence stress relieve and the development of positive coping strategies.

In conclusion, the population of pediatric patients with chronic and complex health conditions is rising fast, resulting in an urgent call for a patient-centered care model, that focuses on the whole person. Demonstrating the feasibility of the proposed intervention could have a significant impact on health promotion and may be a critical step toward the advancement of care modalities aimed at improving coping strategies to mitigate the effects of physical and emotional distress associated with the diagnosis and treatment of all sort of clinical conditions.

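### The only described post-treatment DASS-21 and patient feedback are tied to session 8, with no route for patients who stop earlier

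*Protocol article*

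**What the plan says.** All places are in the protocol article.

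- **Baseline.** Recruitment, screening, and enrollment: "In the first session, patients will be asked to complete a baseline symptomatology assessment". The Session 1 description makes it an online questionnaire done as a home exercise.
- **Post-test and feedback.** Session 8: "Participants will be asked to complete a post-treatment online questionnaire to evaluate symptoms of depression, anxiety and stress and provide feedback". This is the only place where feedback from patients is mentioned.
- **Fidelity form.** Table 2, item 13: "Was the post-test DASS answered right after the final session". The end of the last session is thus the prescribed moment, and it is recorded as a fidelity item.
- **Schedule elsewhere.** The abstract's Methods paragraph has symptoms measured "at baseline and immediately at post-treatment". The limitations in the Discussion say "we will be assessing outcomes only at immediate post-intervention".
- **Analysis.** Data analysis: "The comparisons will be made with ANOVA repeated measures analysis", or non-parametric equivalents. The same section expects 40 recruited to yield 30 who complete.

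The article describes no contact with a patient who stops before session 8.

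**The concern.** Whether a patient's outcome is measured depends on whether that patient stays in the programme. If staying is related to how the patient feels or to how much the sessions help, those with a post-test are a selected group, and their mean change does not describe everyone who started. The Discussion says these exploratory results will inform the prospects of a future trial, so a change that is too favourable could carry over into its planning. The listed limitations cover the missing control group, small sample, measurement bias, short follow-up and mixed sample, but not attrition.

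The second loss concerns the study's main question. Retention figures show how many patients stopped, not why. The only feedback described comes from those who reached the last session, and no reason for stopping is described as collected. A later analysis plan cannot recover answers that were never requested.

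**Working it through.** **1. The article's own figure.** Inputs from Data analysis: 40 recruited, 30 completing. Implied loss = 1 − 30/40 = 25%, or 40 − 30 = 10 patients. Inflating back, 30/(1 − 0.25) = 40, which matches. The 25% is implied and not stated, so this is only a consistency check.

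**2. Who has a post-test.** Session 8, Table 2 item 13, the abstract and the Discussion all put the single post-treatment assessment at the end of the programme. A patient who misses some sessions but attends session 8 still contributes. A patient who stops earlier has no described post-test. On the article's expectation that is about 10 of 40. The number is approximate: some of the 10 may leave in the 1 to 4 weeks between enrolment and session 1 and so lack a baseline too, and some may reach session 8 without returning the form.

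**3. What the analysis uses.** With two time points, repeated-measures ANOVA and its usual non-parametric equivalents need both values. About 30 pairs would be analysed.

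**4. Possible size of the selection effect.** The article gives no expected DASS change, so the result is expressed relative to the completers' change. Let r be the share with a post-test, and let patients who stop change by k times the completers' change. Then

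change over everyone ÷ completers' change = r + (1 − r) × k.

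With r = 0.75 and k assumed:

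| Assumed change in patients who stop (k) | Calculation | Ratio | Completers' figure ÷ figure for everyone |
|---|---|---|---|
| Same as completers (1) | 0.75 + 0.25 × 1 | 1.00 | 1.00 |
| Half as much (0.5) | 0.75 + 0.25 × 0.5 | 0.875 | 1.14 |
| None (0) | 0.75 + 0.25 × 0 | 0.75 | 1.33 |
| Worsen by half as much (−0.5) | 0.75 − 0.25 × 0.5 | 0.625 | 1.60 |

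**5. Precision.** The 95% half-width for a mean change, in SDs of the change, is t(0.975, n − 1)/√n: 0.32 with 40 pairs and 0.37 with 30. The loss of precision is small. What matters is who is missing, not how many.

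**The case against.** **The analysis set is not stated.** This stands. A reader might take the Data analysis phrase "those who completed the program with complete measurements collected" as defining a completers-only DASS population. It does not: it belongs to the sentence on feasibility, which compares eligible, enrolled and completing patients. That the DASS comparison would in effect rest on completers follows from the schedule and the two-time-point method, and must be called an inference.

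**Silence is not a prohibition.** The article condenses a fuller protocol, and the form is online, so early stoppers could be sent it. That is fair, and the Discussion's remark about immediate assessment is mainly about missing long-term follow-up. But several places name the end of the programme as the assessment point and none names another. Followed as written, the plan does not collect these data.

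**The outcome is exploratory and already caveated.** This stands and limits the weight of the point. A reader might infer that the primary outcome is undermined. It is not: the rates of recruitment, retention and participation, and the instructors' fidelity form, need no post-test from those who stop. Patient feedback is not a defined outcome either.

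**The direction and size of bias are assumed.** This also stands. Patients may stop because of illness or appointments, unrelated to benefit, and then the bias could be nil. A reader might quote an overstatement of one third as the result, but it holds only if those who stop do not change at all. Nor should the 10% retention threshold be used to project a handful of pairs: that threshold is a separate matter, and the plan expects 30 completers.

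**Some of the recording already exists.** Table 2 has separate items for sessions missed, programme finished and post-test answered, so no new count is needed.

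**Conclusion.** The point holds as a data-collection weakness of moderate weight. The plan as written gives about 10 of 40 patients no route to a post-test or to feedback. The exploratory DASS change may therefore be too favourable. At 75% retention, the change over everyone runs from equal to the completers' change down to 0.75 of it as the assumed change in those who stop goes from the same to none, and to 0.625 if they worsen by half as much. These ratios rest on the implied 25% loss and on assumed changes; the article supplies neither a DASS effect nor reasons for stopping.

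For a feasibility study the missing account of why patients stopped is the more important loss. The documents do not support saying that a completers-only analysis is prescribed, that bias is shown, or that the primary feasibility rates are affected.

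**What to change.** - Keep the session 8 post-test and feedback for patients who finish.
- For any patient with a baseline who stops early and has not withdrawn from contact, send the same online DASS-21, the feedback form and a reason-for-stopping question, at stopping or at the scheduled end of that patient's programme, with one reminder. A single calendar date for everyone, such as week 4, would not do: sessions may be rescheduled, and Table 2 item 10 allows for patients with fewer than 8 sessions by then, who would be tested mid-programme.
- Analyse the pre-post change in all patients with a post-test, whatever number of sessions they attended, and show the programme completers' result as secondary.
- Report the number and baseline scores of patients without a post-test, and add attrition to the limitations.

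A mixed model is optional. With two time points and similar baselines it would return roughly the completers' change unless data from early stoppers are actually collected, and it does not remove dropout that depends on the outcome.

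Cost: a change of wording, an extra online link and reminder, and a little follow-up work. Some patients who stop will not answer, those without a baseline still cannot enter the pre-post comparison, and early stoppers' post-tests will differ slightly in timing.
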